### Outcomes {12}

The outcomes of this trial are designed to capture both the direct effects of Self-Help Plus (SH+) on maternal mental health and potential intergenerational effects on preschool-aged children. Guided by the study’s conceptual model, outcomes are organized into four categories: (i) the primary outcome, capturing maternal psychological distress; (ii) the key secondary outcome, capturing parent-reported child psychosocial wellbeing; (iii) secondary outcomes, capturing broader maternal mental health and functioning, parenting practices, and additional child psychosocial outcomes; and (iv) exploratory outcomes, capturing ancillary domains that will be analyzed and reported in separate planned publications. Primary, key secondary, and secondary outcomes will be collected at baseline (T0), 3 months post-intervention (T1), and 12 months post-intervention (T2). At baseline, sociodemographic and other potential confounding variables will be collected to describe the sample, a subset of which will be controlled for in statistical analyses (see the “Statistical methods for primary and secondary outcomes {20a}” section); these variables are detailed in Supplementary Table S1. The 12-month follow-up (T2) serves as the primary endpoint for the primary and key secondary hypotheses; outcomes measured at T1 will be analyzed as supportive time points to characterize trajectories. All primary, key secondary, and secondary outcomes will be analyzed as continuous total scores. Prespecified exploratory outcomes (including socio-behavioral skills, cognitive development, and other ancillary domains) are not part of the confirmatory testing strategy and will be reported in separate planned publications (see Supplementary Table S2).

#### Primary outcome

The primary outcome is maternal psychological distress assessed at 12 months post-intervention (T2), measured using the Kessler-6 (K6) [17], a 6-item scale assessing non-specific symptoms of depression and anxiety over the past 30 days. Each item is scored on a 0–4 Likert scale (0 = “none of the time” to 4 = “all of the time”), with total scores ranging from 0 to 24; higher scores indicate greater distress.

#### Key secondary outcome

The key secondary outcome is parent-reported child psychosocial wellbeing assessed at 12 months post-intervention (T2) using the Kiddy-KINDL^R^ (parent-report version) [18], a 24-item instrument assessing emotional wellbeing, self-esteem, family and peer relationships, and daily functioning. Consistent with KINDL scoring conventions, the total health-related quality-of-life score is computed from the 20 non-school items ranging from 1 (“never”) to 5 (“all of the time”), and transformed to a 0–100 scale, where higher scores indicate greater wellbeing.

Both instruments have demonstrated good reliability in prior studies and were linguistically adapted for use in Juba Arabic through standardized forward–backward translation.

#### Secondary outcomes

##### Maternal mental health and functioning

Depression: Assessed with the 9-item Patient Health Questionnaire (PHQ-9) [28]. Each item is scored on a 4-point Likert scale from 0 (“not at all”) to 3 (“nearly every day”), with total scores ranging from 0 to 27. Higher scores indicate more severe depressive symptoms.

Anxiety: Assessed with the 7-item Generalized Anxiety Disorder scale (GAD-7) [29]. Each item is scored on a 4-point Likert scale from 0 (“not at all”) to 3 (“nearly every day”), with total scores ranging from 0 to 21. Higher scores indicate greater anxiety symptom severity.

Post-traumatic stress symptoms: Measured using the 6-item PTSD Checklist–Civilian Version (PCL-C) [30]. Each item is rated on a 5-point scale from 1 (“not at all”) to 5 (“extremely”), yielding a total score between 6 and 30. Higher scores reflect greater severity of post-traumatic stress symptoms.

Perceived stress: Assessed using the 4-item Perceived Stress Scale (PSS-4) [31]. Items are scored on a 5-point scale from 0 (“never”) to 4 (“very often”), with two items reverse-coded. Total scores range from 0 to 16, with higher scores indicating greater perceived stress.

Subjective wellbeing: Measured with the 5-item WHO Well-Being Index (WHO-5) [32]. Each item is rated on a 6-point scale from 0 (“at no time”) to 5 (“all of the time”). The raw total score is multiplied by 4 to yield a final standardized score from 0 to 100, with higher scores representing greater psychological wellbeing.

Functional impairment: Assessed using the 12-item WHO Disability Assessment Schedule 2.0 (WHODAS 2.0) [33]. Items assess difficulties in six domains of functioning, each rated from 0 (“none”) to 4 (“extreme or cannot do”). Higher total scores, ranging from 0 to 48, indicate greater functional impairment.

Psychological flexibility: Assessed with the 7-item Acceptance and Action Questionnaire-II (AAQ-II) [34]. Items are scored on a 7-point Likert scale from 1 (“never true”) to 7 (“always true”) and reverse-coded so that higher total scores (ranging from 7 to 49) indicate greater psychological flexibility.

##### Child wellbeing and functioning

Emotional and behavioral problems: Measured using the parent-reported 17-item Pediatric Symptom Checklist (PSC-17) [35]. Items are rated on a 3-point scale (0 = “never a problem”, 1 = “sometimes a problem”, 2 = “often a problem”), with total scores ranging from 0 to 34. Higher scores indicate greater emotional and behavioral difficulties.

Self-reported psychosocial wellbeing: Assessed with the 12-item child-report version of the Kiddy-KINDL^R^ [36]. Each item is rated on a 3-point Likert scale from 1 (“never”) to 3 (“very often”), with total scores ranging from 12 to 36. Higher scores reflect greater psychosocial wellbeing as perceived by the child.

##### Parenting practices

Positive parenting: Measured using the 6-item Positive Parenting Subscale of the Alabama Parenting Questionnaire (APQ) [37]. Each item is rated on a 5-point scale from 1 (“never”) to 5 (“always”). Higher total scores, ranging from 6 to 30, indicate more frequent engagement in positive parenting behaviors.

Disciplinary practices: Measured with the 11-item Discipline Module from the UNICEF Multiple Indicator Cluster Surveys (MICS6) [38]. This module consists of 11 questions about the frequency of violent and non-violent disciplinary actions taken by caregivers in the past month. Items are rated from 0 (“never”) to 3 (“three or more times”), producing a total score between 0 and 33. Higher scores indicate greater overall use of disciplinary methods.

Table 1 provides a summary of the primary, key secondary, and secondary outcome measures, and Fig. 1 presents the schematic timeline of enrollment, interventions, and assessments.

**Table 1 Tab1:** Primary, key secondary, and secondary outcomes for the SEED trial

Outcome	Instrument	Follow-up	
		**T1**	**T2**

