### Objectives {7}

The Self-Help Plus to Enhance Early Development (SEED) trial seeks to determine whether Self‑Help Plus (SH+) produces sustained mental‑health benefits for war-exposed displaced mothers and generates intergenerational gains for their preschool‑aged children. The primary outcome is maternal psychological distress (Kessler-6) at 12 months post-intervention (T2). The key secondary outcome is parent-reported child psychosocial wellbeing (Kiddy-KINDL^R^ Parent Report) at T2. Secondary outcomes include additional indicators of maternal wellbeing and mental health indicators, parenting practices, and child psychosocial outcomes assessed across study time points (including child self-reported wellbeing and psychosocial functioning). A range of exploratory outcomes, including socio-behavioral skills (patience, risk tolerance, and prosociality), cognitive development, social capital, household wellbeing (e.g., food security), and other ancillary domains, will be analyzed and reported in separate planned publications.

Primary hypothesis:

H1—Maternal mental health: Mothers in SH+ villages will report lower psychological distress (Kessler‑6) [17] at 12 months than mothers in EUC villages.

Key secondary hypothesis:

H2—Child well‑being: Children whose mothers receive SH+ will exhibit higher psychosocial well‑being (Kiddy‑KINDL^R^ - Parent Report) [18] at 12 months than children in EUC villages.

Secondary hypotheses (supportive outcomes):

In addition to the primary and key secondary outcomes, we will assess the impact of SH+ on three secondary domains, each addressed by the following hypotheses:
H3a—Maternal mental health and functioning: SH+ will reduce maternal depression, anxiety, general stress, posttraumatic stress symptoms, and functional impairment at 12 months, relative to EUC.H3b—Parenting practices: SH+ will enhance positive parenting practices and reduce harsh discipline at 12 months, relative to EUC.H3c—Child wellbeing and functioning: SH+ will reduce children’s emotional and behavioral problems and improve their self-reported psychosocial wellbeing at 12 months, relative to EUC.

A detailed description of the primary, key secondary, secondary, and exploratory outcomes is provided in the “Outcomes {12}” section, below.

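### The discipline score for H3b adds violent and non-violent methods together, so it does not isolate the harsh discipline that the hypothesis is about

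*Protocol article*

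**What the plan says.** Objectives {7} states H3b as: "SH+ will enhance positive parenting practices and reduce harsh discipline at 12 months, relative to EUC".

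The Parenting practices part of Outcomes {12} names two measures. One is the positive parenting subscale of the APQ. The other is the discipline module, described as follows: "This module consists of 11 questions about the frequency of violent and non-violent disciplinary actions taken by caregivers in the past month". On scoring: "Items are rated from 0 (“never”) to 3 (“three or more times”), producing a total score between 0 and 33". On meaning: "Higher scores indicate greater overall use of disciplinary methods".

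The opening paragraph of Outcomes {12} sets the form of analysis: "All primary, key secondary, and secondary outcomes will be analyzed as continuous total scores".

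Table 1 lists disciplinary practices once, as the 11-item module, with no division into violent and non-violent items.

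**The concern.** The hypothesis concerns one kind of discipline, and the score counts both kinds. A mother who uses less violent discipline and correspondingly more non-violent discipline has done what H3b hopes for, yet her total need not move. A mother who cuts back only on non-violent discipline lowers her total and so appears to support H3b.

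The stake is how the parenting result is interpreted. The Discussion presents parenting practices as a possible route from maternal distress to child outcomes. If the discipline result is flat, a reader could not tell whether harsh discipline was unchanged or whether two opposite changes offset each other. If the total falls, a reader could not tell which kind of discipline fell.

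This is not a detail left to an analysis plan. The article itself fixes the instrument, the item scoring, the range, the meaning of the score and the use of totals. An analysis plan with a violent-only score would depart from what the article says.

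**Working it through.** **1. The plan's own range.** Inputs from Parenting practices: 11 items, each scored 0 to 3. Minimum 11 × 0 = 0; maximum 11 × 3 = 33. The stated 0–33 reproduces, so all 11 items enter the sum.

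**2. Sign of the items.** The range alone does not settle this, because reversing the non-violent items would also give 0–33. The sentence on meaning settles it: a total with reversed items would not measure overall use of disciplinary methods. The article also says so where it does reverse items (PSS-4 and AAQ-II), and says nothing of the kind for this module.

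**3. Is harsh discipline measured elsewhere?** The other parenting outcome is the APQ positive parenting subscale. It serves the first half of H3b and does not measure harsh discipline. No violent-item subscore is defined anywhere in the article.

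**4. Condition for cancellation, in raw points.** Let k of the 11 items be non-violent. Then

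change in total = (11 − k) × mean change per violent item + k × mean change per non-violent item.

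The article does not give k, so it is varied. Assume each violent item falls by 0.3 points. The total is unchanged if each non-violent item rises by 0.3 × (11 − k) / k:

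- k = 2: 0.3 × 9 / 2 = 1.35
- k = 3: 0.3 × 8 / 3 = 0.80
- k = 4: 0.3 × 7 / 4 = 0.53
- k = 5: 0.3 × 6 / 5 = 0.36

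All of these are possible on a 0–3 item.

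**5. Standardized effect on the total.** Assumptions, none from the article: equal item SDs (set to 1), correlation 0.3 between items of the same kind, and no correlation between the two kinds. With v = 11 − k violent items:

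- variance of the violent sum: V = v + v(v − 1) × 0.3
- variance of the non-violent sum: N = k + k(k − 1) × 0.3
- effect on the total = (dV × √V + dN × √N) / √(V + N)

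Example, k = 3: V = 8 + 56 × 0.3 = 24.8 and N = 3 + 6 × 0.3 = 4.8, so √V = 4.98, √N = 2.19 and √29.6 = 5.44. With dV = −0.20 and dN = +0.30, the effect is (−0.996 + 0.657) / 5.44 = −0.06.

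| k | V | N | dV −0.20, dN 0 | dV −0.20, dN +0.30 | dV 0, dN −0.20 |
|---|---|---|---|---|---|
| 2 | 30.6 | 2.6 | −0.19 | −0.11 | −0.06 |
| 3 | 24.8 | 4.8 | −0.18 | −0.06 | −0.08 |
| 4 | 19.6 | 7.6 | −0.17 | −0.01 | −0.11 |
| 5 | 15.0 | 11.0 | −0.15 | +0.04 | −0.13 |

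The first effect column is dilution. The second shows partial to full cancellation, with reversal at k = 5. The third shows a fall in non-violent discipline alone moving the score in the direction H3b predicts.

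**The case against.** The strongest reply has four parts.

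- **The total still carries information on H3b.** If SH+ changes only violent discipline, the score moves the right way and loses little. This stands. A reader might infer that H3b's discipline half cannot be tested at all, and the article does not support that: what is lost is specificity.
- **Cancellation is hypothetical.** Nothing in the article says that SH+, a stress-management course, raises non-violent discipline. A mother already at the top category on the non-violent items could not offset a fall in the violent ones. This also stands. It limits how likely or how large cancellation is, but does not remove the possibility, which follows from the stated scoring.
- **The direction of benefit is not undefined.** The article says what a higher score means and H3b predicts a reduction, so a lower total is implicitly favourable. That is a fair reading. The difficulty is that a lower total is favourable for H3b only when it comes from the violent items.
- **The stakes are limited.** Objectives {7} labels these hypotheses supportive, and Sample size {14} says secondary outcomes do not determine trial success. The Discussion calls parenting a potential pathway, and the statistical sections specify no mediation model that uses this score. This lowers the priority of the point but does not resolve the mismatch.

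**Conclusion.** The hypothesis and its outcome do not match. H3b concerns harsh discipline; the only discipline score measures discipline of any kind and is fixed for analysis as a total. That conclusion rests on the article's wording alone.

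The size rests on assumptions about the item split, the item correlations and the effects. Under those used here, the loss ranges from slight dilution to a change of sign. The figures are illustrations, not forecasts, and a reader should not infer that cancellation is expected in this trial.

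This is a worthwhile correction to one supportive secondary outcome, not a threat to the trial's main conclusions. The K6 test, the fixed sequence to the parent-reported Kiddy-KINDL and the sample size are untouched.

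**What to change.** Before the 12-month data are analyzed:

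- Prespecify the sum of the violent items only, lower being better, as the H3b discipline outcome. List which items it contains. Its range is 0 to 3 × the number of violent items (for example 0–24 if there are 8).
- Report the non-violent items as a separate score.
- Keep the 11-item total as descriptive only, so that no prespecified outcome is deleted.
- Amend the discipline paragraph under Parenting practices, the sentence in Outcomes {12} on total scores, and the discipline row of Table 1.

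The cost is scoring and wording. The items are rated one by one, so no new data are needed. Trial status reports baseline complete and 12-month follow-up ending in February 2027. The change can therefore still be made before the 12-month results are known; made afterwards, it would look data-driven.

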**Primary outcome:**			
Maternal psychological distress	Kessler Psychological Distress Scale (K6) [17]	X	X
**Key secondary outcome:**			
Child psychosocial wellbeing (parent-report)	Kiddy-KINDL^R^ - Parent Report [18]	X	X
**Secondary outcomes:**			
**Maternal mental health**			
Depression	Patient Health Questionnaire-9 (PHQ-9) [39]	X	X
Anxiety	Generalized Anxiety Disorder 7-item scale (GAD-7) [29]	X	X
Post-traumatic stress	Post-Traumatic Checklist 6-item Civilian Version (PCL-C) [30]	X	X
Perceived stress	Perceived Stress Scale 4-item version (PSS-4) [31]	X	X
**Maternal wellbeing and functioning**			
Subjective wellbeing	WHO-5 Well-Being Index [32]	X	X
Functional impairment	15-item version of the World Health Organization Disability Assessment Schedule 2.0 (WHODAS-II) [40]	X	X
Psychological flexibility	Acceptance and Action Questionnaire - version 2 (AAQ-2) [34]	X	X
**Child wellbeing and functioning**			
Emotional and behavioral problems	Pediatric Symptom Checklist (PSC-17) [35]	X	X
Psychosocial wellbeing (self-report)	Kiddy-KINDL^R^ – self-report [36]	X	X
**Parenting practices**			
Positive parenting	6-item Positive Parenting Subscale of the Alabama Parenting Questionnaire (APQ) [37]	X	X
Disciplinary practices	11-Item Discipline Module of the Multiple Indicator Cluster Surveys (MICS) [38]	X	X

**Fig. 1 Fig1:**
[figure not shown]
SPIRIT schedule of enrollment, interventions, and assessments for the SEED trial

#### Exploratory outcomes

To provide a richer understanding of the intervention’s impact, data on several exploratory and contextual variables will be collected. These include measures of food security (Food Insecurity Experience Scale (FIES)) [41, 42], household dietary diversity (HDDS) [43], child malnutrition (height-for-age *z*-score (HAZ)) [44, 45], and social capital (group membership, participation, and trust). These will be assessed at all three timepoints (T0, T1, T2), except HAZ, which will be measured only at T0 and T2. In addition, socio-behavioral skills will be assessed at baseline (T0) and 12 months (T2) using incentivized tasks: patience is measured with an investment task adapted from Andreoni and Sprenger [46]; risk tolerance with a bomb risk-elicitation task adapted from Crosetto and Filippin [47]; and prosociality with four binary allocation games adapted from Fehr and colleagues and Bauer and colleagues [48, 49]. We will also assess child cognitive skills, including mathematics ability (free counting, number comparison, Give-N, addition/subtraction tasks) [50], language ability (TIFALDI) [51], spatial ability (TOSA) [50], and theory-of-mind (“surprise outcome” and “surprise content” tasks) [52, 53] at baseline (T0) and the 12-month follow-up (T2). All exploratory instruments and tasks will be culturally adapted and pilot-tested during a 5-day training in Arua with Juba Arabic–speaking research assistants; enumerators receive supervised practice (including role-plays and field piloting with mother–child dyads) to standardize administration before data collection. Supplementary Table S2 provides an overview and description of exploratory outcomes and measures. These exploratory outcomes are not part of the confirmatory testing strategy and will be reported in separate, dedicated analyses.

### Participant timeline {13}

The SPIRIT participant flow diagram is shown in Fig. 2. Baseline data will be collected immediately after participants complete screening, provide informed consent, and are enrolled in the study. All participants will then receive a single session of Enhanced Usual Care (EUC) before randomization. Those assigned to the intervention arm will then participate in the Self-Help Plus (SH+) program, which consists of five weekly group sessions. Follow-up assessments will be conducted at 3 and 12 months post-intervention.

**Fig. 2 Fig2:**
[figure not shown]
SPIRIT flow diagram of the phases of the SEED trial

### Sample size {14}

We determined the required sample size using *PowerUp!* [54], focusing on the primary outcome of maternal psychological distress (Kessler-6) [17] at the 12-month follow-up. Calculations were based on a two-arm cluster-randomized design with equal allocation and equal expected cluster sizes.

Our objective is to achieve 90% statistical power to detect a minimal clinically important difference (MCID), defined as Cohen’s *d* = 0.20, for the primary outcome using a two-tailed significance level (*α*) of 0.05. The parent-reported Kiddy-KINDL^R^ at T2 is specified as a key secondary outcome and will be tested using a hierarchical fixed-sequence procedure: K6 will be tested first at *α* = 0.05, and Kiddy-KINDL^R^ will be formally tested at *α* = 0.05 only if the primary test is statistically significant. This approach controls the overall Type I error rate across the primary and key secondary outcomes without requiring alpha adjustment of the individual tests [55]. While modest, an effect size of this magnitude (*d* = 0.20) is meaningful for a low-intensity, scalable intervention delivered by lay facilitators. In high-burden humanitarian settings, even small average improvements in psychological wellbeing can translate into substantial population-level benefits and policy relevance [56].

For the power calculation, we used an intra-cluster correlation coefficient (ICC) of 0.012, based on the values observed in the earlier SH+ cluster-RCT in the same setting and population [14]. The SH+ intervention is designed for delivery in groups of up to 30 individuals. To account for potential attrition over the 12-month study period, we conservatively assume a 20% dropout rate. Consequently, we plan to recruit 30 mother–child dyads per cluster, with an expected 24 analyzed per cluster at endline. Based on these parameters (power = 0.90, *α* = 0.05, *d* = 0.20, ICC = 0.012, *m* = 24 analyzed per cluster), *PowerUp!* indicates that 24 clusters (12 per arm) are required. This yields a total target sample of 720 mother–child dyads across 24 villages within Rhino Refugee Settlement.

These calculations are conservative, assuming no variance reduction from baseline adjustment. Because the primary analyses will control for baseline outcome values and cluster-level covariates, realized statistical power is expected to be at least as high as the nominal estimate. Secondary outcomes are not used to determine trial success and are not specifically powered; however, under the same design parameters, this sample size provides reasonable power to detect small-to-moderate effects for continuous secondary outcomes.

We will document actual cluster sizes, attrition, and observed ICCs during implementation and report effect estimates with 95% confidence intervals to reflect the precision achieved.

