A key scope consideration is the role of fathers. Intergenerational socialization occurs within families, and fathers (and other caregivers) can shape children’s preferences, behaviors, and wellbeing. The present trial, however, targets mothers and does not directly intervene with—or systematically measure outcomes for—fathers. As a result, our inferences focus on maternal pathways; any household-level spillovers that involve fathers cannot be isolated with these data. This design choice reflects the study’s primary aim and operational constraints in this setting, but it also identifies an important direction for future research: testing paternal and two-caregiver pathways, and examining whether combined or family-based approaches amplify or modify effects.

The findings from this trial will inform humanitarian policy and future research. Evidence of lasting and intergenerational benefits would provide a powerful rationale for scaling up SH+ as a cost-effective approach to build resilience in crisis-affected families. However, if the effects fade over time or do not extend to children, this would also be an important finding suggesting that a brief intervention like SH+ may not be enough on its own to produce long-term change. This would guide the next phase of research, pointing towards the need to test additional support such as follow-up “booster” sessions to maintain maternal gains, or combining SH+ with specific parenting programs to better support child development.

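### The sample-size inputs as stated give about 53% unadjusted power for d = 0.20, not 90%; 24 villages reach 90% only at d = 0.32

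*Protocol article*

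**What the plan says.** The protocol article, Sample size {14}, sets the target: "Our objective is to achieve 90% statistical power to detect a minimal clinically important difference (MCID), defined as Cohen’s *d* = 0.20". The test is two-sided at the 5% level, on K6 at 12 months. The design has two arms, equal allocation and equal expected cluster sizes. For clustering, "we used an intra-cluster correlation coefficient (ICC) of 0.012, based on the values observed in the earlier SH+ cluster-RCT". Thirty dyads are to be recruited per cluster and, after 20% dropout, 24 analysed. From these inputs the section reports that PowerUp! "indicates that 24 clusters (12 per arm) are required", giving 720 dyads recruited.

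The same section then comments on the result: "These calculations are conservative, assuming no variance reduction from baseline adjustment". Because the primary analyses will adjust for baseline values and cluster-level covariates, "realized statistical power is expected to be at least as high as the nominal estimate".

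**The concern.** Every input needed to check the calculation is printed, including the absence of any covariate gain, so the result does not depend on an unseen analysis plan. A rough check already fails. An individually randomised comparison of means at d = 0.20 with 90% power needs 526 per arm before any allowance for clustering, and this plan expects to analyse 12 × 24 = 288 per arm.

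What is at stake is the trial's stated ability to detect its own minimal clinically important difference on the primary outcome. K6 is also the gate in the fixed sequence, so any shortfall there carries over to the chance that the child wellbeing outcome is formally tested. A reader who takes 90% at face value would give a non-significant K6 result more weight than the design can bear.

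**Working it through.** **Inputs (all from Sample size {14}).** d = 0.20 on a scale with SD 1; two-sided alpha 0.05; ICC 0.012; m = 24 analysed per cluster; J = 24 clusters in total, 12 per arm; no variance reduction from covariates.

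**Attempt to reproduce the stated 90%.** For a two-level cluster-randomised design with equal allocation:

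SE = √[4 × (ICC + (1 − ICC)/m) / J]
= √[4 × (0.012 + 0.988/24) / 24]
= √[4 × 0.05317 / 24] = √0.00886 = 0.0941

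d/SE = 0.20/0.0941 = 2.12

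- Noncentral t with J − 2 = 22 df: power 52.9%.
- Normal approximation: Φ(2.125 − 1.960) = 56.5%.
- Simulation of cluster means compared by t-test, 40,000 runs: 53.5%.

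The stated 90% is not reproduced.

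**Detectable effect with the planned design (t, 22 df).**

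- 80% power: (2.074 + 0.858) × 0.0941 = 0.276.
- 90% power: (2.074 + 1.321) × 0.0941 = 0.320. Simulated power at d = 0.32 is 90.4%.

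**Clusters needed for 90% at d = 0.20.** Design effect = 1 + 23 × 0.012 = 1.276. Analysed per arm = 526 × 1.276 ≈ 671, so 2 × 671/24 ≈ 56 clusters by the normal approximation. The t-based search gives 58, or 58 × 24 = 1,392 analysed.

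**Does any other reading of the inputs give 90% with 24 clusters at d = 0.20?**

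| Change to the stated inputs | Power |
|---|---|
| No dropout, m = 30 | 60% (t), 64% (normal) |
| ICC = 0, m = 24 | 67% (normal) |
| ICC = 0 and m = 30 | 77% (normal) |
| One-sided 0.05, m = 24 | 66% (t), 68% (normal) |
| One-sided 0.05, m = 30 | 72% (t), 75% (normal) |

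None does. Rounding and the choice of t or normal cannot explain the gap. One combination that does come close is 24 clusters per arm (48 in total) with m = 30, at 89% (t) or 90% (normal). That would fit a per-arm count read as a total with dropout left out, but it is conjecture: the article says plainly that 24 is the total.

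**Effect of baseline adjustment.** The article gives no R², so the values here are assumptions, taken as equal at individual and cluster level. The SE is multiplied by √(1 − R²), with 22 df kept.

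| Assumed R² at both levels | Power at d = 0.20 (t) |
|---|---|
| 0 | 53% |
| 0.2 | 62% |
| 0.3 | 68% |
| 0.4 | 75% |
| 0.5 | 82% |
| 0.61 | 90% |

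If baseline K6 were the only source of the gain, R² = 0.61 would mean a correlation between baseline and 12-month K6 of about √0.61 = 0.78.

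**The case against.** The strongest reply is that 53% is not the power of the planned analysis. Statistical methods {20a} adjusts the primary comparison for baseline K6, and adjustment generally raises power. That stands, and it limits what can be claimed. A reader might infer that the trial has at most a 53% chance of detecting its target, that it is a coin flip, or that it carries a 47% false-negative rate. The documents do not support any of these, because all three treat the unadjusted figure as a ceiling. The reply does not rescue the 90%, however: the Sample size section says adjustment played no part in obtaining it.

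It can also be said that calling the calculation conservative is right in direction, since ignoring adjustment does understate power. That also stands. The fault is in the nominal figure to which the assurance is attached.

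Two further inferences should be resisted. One is a joint power for the maternal and child hypotheses. The article gives no effect size or ICC for the Kiddy-KINDL and no correlation between the two outcomes, so any such figure would rest on invented inputs. The other is that the Discussion intends to read a non-significant test as a faded effect. Its words are "However, if the effects fade over time or do not extend to children, this would also be an important finding". That sentence is conditional on effects, not on a p-value, and the Sample size section already commits to reporting 95% confidence intervals. The Discussion is not an instance of this error.

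Finally, neither the effect estimate, nor its interval, nor type I error control depends on the power statement.

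**Conclusion.** The power statement is wrong on its own inputs. Unadjusted power for d = 0.20 is about 53% (57% by the normal approximation) against a stated 90%, a gap of about 37 percentage points on the t-based figure. The design has 80% power at d = 0.28 and 90% at d = 0.32. This rests only on the printed inputs and the standard two-level formula.

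Power of the baseline-adjusted analysis cannot be fixed from the article. For an assumed R² of 0.2 to 0.5 at both levels it is about 62% to 82%. It reaches 90% only at about 0.61, for which the article offers no evidence. The expectation that realised power will be at least nominal is therefore unsupported while nominal means 90%; it becomes reasonable once nominal means 53%.

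**What to change.** Correct the text of Sample size {14}, and note the correction in the protocol and registry record:

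- State that 24 clusters with 24 analysed each, ICC 0.012, two-sided alpha 0.05 and no adjustment give about 53% power for d = 0.20, 80% for d = 0.28 and 90% for d = 0.32.
- Add power for the baseline-adjusted analysis over a stated range of R², labelled as an assumption, with any source the sponsor has for it.
- Reword the sentences on conservatism and realised power so that they refer to the corrected unadjusted figure and no longer imply at least 90%.
- State in advance that a non-significant K6 result whose 95% confidence interval still includes a 0.20 SD benefit is inconclusive, not evidence that the effect has faded.

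No added enrolment is proposed. Trial status reports that recruitment and baseline data collection were completed on 12 December 2025, with final follow-up expected in February 2027, so the correction can be made before the 12-month results are known. Conduct and analysis do not change. The cost is a text amendment and a less favourable published power figure.
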